**Fig. 1 Fig1:**
[figure not shown]
Trial Flow Chart

### Sample size

Sample size estimation is based on monthly frequency of WPV. Using the study by I. et al., (2004), we set a significant change of 12.1% (decreased from 17.8% by 5.70%), alpha error of 0.05, beta error of 0.20, the estimated number (N _simple_) of monthly records is 29 per group for simple randomized control trial [47]. The intra-class correlation coefficients (ICC), explains the inflation factor of cluster randomized controlled design trial, is set as 0.05 in proposed study [48]. Based on the numbers of wards of MZ and HZ (*n* = 8), the minimum number of 6-month follow-up record (m) is 48. The sampling size of cluster randomized controlled trial (N _cluster_) is calculated as: N _cluster_ = [1 + (m^− 1^) * ICC] * N _simple_ ≈ 98. The minimum number of recruited hospitals of each group (N) is calculated as: N = N _cluster_/ m ≈ 2.04 < 3, suggesting at least 3 hospitals per group.

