### Settings and participants

This trial will be conducted among 6 major public psychiatric hospitals in Guangdong, China. The involved psychiatric hospitals are Guangzhou Mental Health Center (GZ), Shenzhen Mental Health Center (SZ), the Third Hospital of Foshan City (FS), the Second Hospital of Huizhou (HZ), Shantou Mental Health Center (ST), and the Third Hospital of Meizhou (MZ). The number of wards (secured and non-secured) and nurses of the involved hospitals are shown in Table 1*.* This study has gained ethical approval from the IRB of GZ. Executives from the involved institutes will be informed and asked for their permission to conduct the study, with the help of the nurses. Informed consent will be obtained from all participants before they complete the surveys.

**Table 1 Tab1:** Numbers of wards and nurses of recruited hospitals (secured and non-secured)

Hospital	Non-secured ward			Secured ward		
	Number of wards	Number of beds	Number of nurses	Number of wards	Number of beds	Number of nurses
GZ	3	120	65	14	865	322
SZ	1	45	18	10	623	297
FS	1	106	29	8	816	243
HZ	1	44	20	7	906	291
ST	3	60	46	8	620	231
MZ	1	60	20	7	700	220

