### Statistical methods

Statistical analysis will be performed using SPSS version 22.0 software (SPSS Inc., Chicago, IL, USA). Descriptive statistics will be reported as frequencies and percentages, if applicable. The Shapiro-Wilk test will be used in order to examine the distributions of the continuous outcomes. Quantitative variables will be presented using means and standard deviations or as the median and interquartile range. A Student’s t-test, Mann-Whitney U test, Chi-square test, or Fisher’s exact test will be adopted to compare the groups according to their normality distributions. Additionally, a repeated ANOVA will be used to explore the effectiveness of the CRSCE training program and further regression analysis will be performed, if appropriate. The statistical significance will be set at *P* < 0.05, two tailed, with a 95% confidence interval (*CI*).

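### The sample size calculation makes no allowance for having only six hospitals: on its own inputs, 3 v 3 gives about 72 to 76% power, not the stated 80%

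*Protocol article*

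**What the plan says.** All of the following is in the Sample size section of the protocol article unless another section is named.

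- Error rates: "alpha error of 0.05, beta error of 0.20". The Statistical methods section makes testing "two tailed, with a 95% confidence interval".
- Unclustered size: the number "of monthly records is 29 per group for simple randomized control trial". No standard deviation is given.
- Clustering: a single intra-class correlation, which "is set as 0.05 in proposed study".
- Cluster size: from the 8 wards of the two smallest hospitals, "the minimum number of 6-month follow-up record (m) is 48", that is 8 wards x 6 months.
- Result: about 98 records per group, and 98/48 = 2.04 hospitals, "suggesting at least 3 hospitals per group".

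The Settings and participants section confirms the number of clusters: "This trial will be conducted among 6 major public psychiatric hospitals in Guangdong, China". The Randomization section allocates whole hospitals 1:1, so the comparison is 3 v 3.

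**The concern.** The design effect converts correlated records into an equivalent number of independent ones, and it does so correctly for any number of clusters. It does not account for how poorly the between-hospital variance is estimated from six hospitals. A hospital-level comparison has 3 + 3 - 2 = 4 degrees of freedom, so the two-sided 5% critical value is 2.776 instead of 1.96. No cluster-level degrees of freedom enter the calculation. The section names no critical value, so the use of large-sample values is inferred from the formula; the two-hospital check below supports that inference.

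At stake is the beta of 0.20 attached to WPV frequency, the primary outcome on which the trial is sized. This section is the article's only justification for the number of hospitals. If the stated beta is not met, a non-significant result would be weighed against more power than the design has.

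**Working it through.** **1. Reproduce the plan's figure.** The design effect is 1 + (48 - 1) x 0.05 = 3.35. Then 3.35 x 29 = 97.15, rounded up to 98, and 98/48 = 2.04, rounded up to 3. The printed exponent on m must mean m - 1, because reading it as 1/m gives only 29.03 records. The chain holds.

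**2. Effect implied by 29 per group.** With two-sided alpha 0.05 and 80% power, (1.960 + 0.842)² = 7.849. The standardised difference is d = sqrt(2 x 7.849/29) = 0.736. If 29 came from a t-test calculation, d = 0.749. Both are carried forward.

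**3. Standard error with 3 v 3 hospitals.** In SD units, the variance of one hospital mean is 0.05 + 0.95/48 = 0.0698. The standard error of the difference is sqrt(2 x 0.0698/3) = 0.2157. The noncentrality is 0.736/0.2157 = 3.41, or 3.47 for d = 0.749.

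**4. Power.**

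| Design (ICC 0.05) | Large-sample critical value | t, 2(k - 1) df |
|---|---|---|
| 2 per arm, m = 48 | 79.5 to 80.9% | 35 to 36% (2 df) |
| 3 per arm, m = 48 | 92.7 to 93.5% | 72.4 to 73.8% (4 df) |

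The first row shows that about 2 hospitals per arm, the plan's 2.04, reaches 80% only with large-sample critical values. Simulated t-tests on hospital means for the second row gave 72.7% and 73.8%.

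**5. Actual ward counts.** In Table 1, secured plus non-secured wards number 17, 11, 9, 8, 11 and 8. Over six months that is 102, 66, 54, 48, 66 and 48 records. The six variances 0.05 + 0.95/m sum to 0.3953. Each arm's mean averages three hospitals, so the standard error is sqrt(0.3953/9) = 0.2096. The noncentrality is 3.51 to 3.57 and power is 74.7 to 76.1%. Weighting hospitals by precision changes this by about 0.1 point, whichever way they are split.

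**6. Detectable difference.** With 4 df, 80% power needs a noncentrality of 3.76. At m = 48, 3.76 x 0.2157 = 0.81 SD, and 0.81/0.736 = 1.10, so the detectable difference is about 10% larger than implied.

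**7. Sensitivity only: stronger correlation between months of one ward.** Suppose different wards of a hospital correlate at 0.05, and months of the same ward at an assumed rho. The design effect at m = 48 is then 1 + 5 x rho + 42 x 0.05.

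| Assumed rho | Design effect | Power, t on 4 df |
|---|---|---|
| 0.05 (plan) | 3.35 | 72 to 74% |
| 0.3 | 4.6 | 59 to 61% |
| 0.5 | 5.6 | 52 to 53% |

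The protocol gives no value for rho. Step 4 does not depend on it.

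**The case against.** Several points on the other side have weight.

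*The single ICC may be right.* A reader might infer that applying 0.05 to repeated months of one ward is itself an error, and that true power is 52 to 61%. The document does not support that. It does not say at which level the 0.05 is defined. If it is the average correlation over all 48 records of a hospital, the design effect of 3.35 is exact whatever the ward structure. For example, 0.30 within wards and about 0.02 between wards also gives 1 + 5 x 0.30 + 42 x 0.0202 = 3.35. Putting 0.3 to 0.5 on top of 0.05 raises the average correlation to 0.077 to 0.098, which is no longer the plan's input. The single ICC contributes nothing to the 72 to 76%.

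*The range is not a ceiling.* A reader might also take 76% as the most the trial can achieve. It is not. The Data collection section has primary outcomes recorded every month, and the Statistical methods section plans a repeated ANOVA and possibly regression. Adjustment for baseline could raise power, but it is not in the calculation and no correlation with baseline is given. Counting nine months of records would give 78 to 79%. An ICC of 0.03 would give about 85 to 86%, but the plan fixes 0.05.

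*Rounding up gives a margin.* Three hospitals supply 3 x 48 = 144 records against 98 needed, or 144/3.35 = 43 effective records against 29. That stands, and it is why power is above 70%. It does not fully offset 4 degrees of freedom.

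*The base figure is unverified.* The 29 cannot be checked without a standard deviation. Read as two proportions, 17.8% v 12.1% needs 614 per group, and 17.8% v 5.7% needs 110. Taking 29 at face value therefore favours the plan.

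**Conclusion.** The point holds. On the plan's own inputs the design has about 72 to 74% power at 48 records per hospital and 75 to 76% with the Table 1 ward counts, so the stated beta of 0.20 is missed by roughly 4 to 8 percentage points. The shortfall comes entirely from the 4 degrees of freedom. It is a fault of method: the design effect and the arithmetic are sound.

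The result assumes N_simple = 29 as given, ICC 0.05, six follow-up months, a two-sided 5% test and an unadjusted comparison of hospital means. The lower figures for stronger same-ward correlation show sensitivity to an assumption and are not a demonstrated error.

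**What to change.** Keep the six hospitals and rewrite the Sample size paragraph:

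1. Recompute power with t on 4 degrees of freedom, preferably with the Table 1 ward counts. Replace the implied 80% with the resulting power, or with the difference detectable at 80% power (about 0.81 SD at m = 48).
2. State the standard deviation or other basis behind the 29, since every later figure rests on it.
3. Say what the ICC of 0.05 refers to. As a sensitivity analysis, show power when months within a ward correlate more strongly than wards within a hospital, using 1 + 5 x rho_ward + 6 x (wards - 1) x rho_hospital. Estimate both correlations from past months in the hospital information systems.
4. State that any gain from baseline adjustment is not included.

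The cost is one rewritten paragraph, an extract of past data for the correlations, and a less favourable stated power. No hospital is added and trial conduct does not change.

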### Randomization

This is a cluster randomized controlled trial. The randomization unit is every involved psychiatric hospital. Involved psychiatric hospitals will be consecutively coded from 1 to 6 by a statistician not actively engaging in this study. By using an online random number generator, hospitals will be assigned to either the intervention or control group according to a 1:1 ratio. The statistician will then inform the research coordinator of the group allocations. Afterwards, the training schedule of each hospital will be designed according to its allocation. To ensure justice, when the intervention group has completed the CRSCE-based program, and follow-up data have been collected, the control group will also receive the same CRSCE-based training.

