Having discovered various factors contributing to WPV, strategies reducing its incidence and negative impacts have been developed accordingly. Occupational Safety and Health Administration (OSHA) guideline indicates that WPV prevention program should be based on the simultaneous implementation of organizational measures, administrative measures, and staff training [24]. Interventions targeted at enhancing staffing levels, restructuring the workplace environments, promoting work organization, improving nurse-patient therapeutic relations, and training medical workers have all proven effective in alleviating WPV [19, 20, 25, 26]. Notably, substantial evidence has found that the promotion of improved de-escalation skills among psychiatric nurses is the most widely acknowledged intervention strategy [22, 27–33]. Experts have reached a consensus that de-escalation (DE) technique is the first-line WPV management strategy during early incidence stages [34, 35]. DE refers to a range of skills involving averting conflicts through emotional regulation and self-management techniques [36]. In the psychiatric nursing context, studies have shed light on the contents of DE. It has been proposed that DE should focus on nurse-patient interactions, patient engagements, choosing appropriate intervention times, ensuring mutual safety, confirming patients’ autonomy, limit-setting, and authoritative interventions [37, 38]. Another study by Hallett and Dickens [39], using concept analysis, emphasized that DE was achieved through techniques around self-regulation, communication, assessment, action, and safety maintenance [39]. The application of DE has had positive impacts on improving nurses’ capacities, as well as on nurse-patient relationships, while reducing the use of coercive strategies by nurses (including seclusion, physical restraints, and mechanical restraints). After comparing pre- and post- results of the De-escalating Aggressive Behavior Scale, Nau et al., [40] suggested that the training of DE enhanced student nurses’ performances in dealing with WPV (with scores for untrained = 3.01 vs. trained = 3.61). Another study also found that nurses receiving DE training possessed greater self-perceived confidence than those without, demonstrating that this form of preparation effectively enhanced nurses’ performances by strengthening their confidence levels in dealing with WPV [41]. In addition, Fröhlich et al., [42] highlighted DE training’s role in helping to cultivate a harmonious atmosphere within psychiatric wards by improving patients’ coherence and subjective safety. Most importantly, the application of DE techniques decreases the use of coercive strategies. Empirical studies verified that DE training, targeting psychiatric nurses, reduced the use of physical restraints by approximately 26.4 to 74.0%, and had cut down their likely duration and resultant adverse effects [43]. Current findings have confirmed that DE is a significantly utilized approach in dealing with WPV as well as in reducing the use of coercion, suggesting that DE is an indispensable component of standardized training programs for psychiatric nurses [29, 41, 44, 45]. However, the presented studies all possesses some limitations. First, among most studies, DE training is combined with other components concurrently, such as improved staffing levels, leadership styles, and risk assessments, and, therefore, the actual efficacy of DE itself remains unclear. Second, studies concerning DE provides weak creditability due to their lack of trial-based evidence [46]. Third, the characteristics of the DE training programs used among the current studies varies from one to another because its design needs to be matched to the environmental and socio-cultural factors— hence, the findings of Western studies might not be accurate in China. Last, very few studies simultaneously appraise the effectiveness of DE training via the improvement of nurses’ capacities and objective indicators.

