### Data collection

Primary outcomes will be continuously collected every month by extracting data from the hospital information systems (HIS) and their annual reports. Secondary outcomes are collected at baseline (T_0_), 3 months after intervention (T_1_, the end of intervention), and 6 months after intervention (T_2_, follow-up). Data collection will be completed by research assistants who are not aware of this study’s design.

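### Six unequal hospitals are allocated 3 v 3 by an unrestricted draw, and no baseline-adjusted primary comparison or pre-training window is fixed

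*Protocol article*

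**What the plan says.** All references are to the protocol article.

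- **Allocation.** Under Settings and participants: "This trial will be conducted among 6 major public psychiatric hospitals in Guangdong, China". Under Randomization: "The randomization unit is every involved psychiatric hospital". The mechanism follows: "By using an online random number generator, hospitals will be assigned to either the intervention or control group according to a 1:1 ratio". No restriction on the draw is mentioned.
- **Hospital characteristics.** Table 1, titled "Numbers of wards and nurses of recruited hospitals (secured and non-secured", lists wards, beds and nurses for each hospital.
- **Staffing as a cause.** The Background counts staffing among the measures shown to alleviate WPV: "Interventions targeted at enhancing staffing levels, restructuring the workplace environments, promoting work organization". It also criticises earlier training studies because staffing changed at the same time.
- **Primary outcomes.** Under Outcomes they are monthly rates per 1,000 patient days. Under Data collection: "Primary outcomes will be continuously collected every month by extracting data from the hospital information systems (HIS) and their annual reports". That section attaches T0, T1 and T2 to the secondary outcomes. The Abstract lists a baseline time point in general terms. No length of pre-training data is given for the primary outcomes.
- **Analysis.** Statistical methods names the t-test, Mann-Whitney, chi-square and Fisher tests for comparing groups, a repeated ANOVA for effectiveness, and regression on a conditional basis. No covariate is named.
- **Sample size.** The calculation counts six months of follow-up records only.

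**The concern.** With three hospitals per arm, a plain draw gives no dependable balance on any hospital characteristic. If the better-staffed hospitals fall together, a reader cannot separate the training from staffing. That is the weakness the Background finds in earlier work. Allocation is done once, before any analysis, so no later analysis plan can undo an unlucky draw; it can only adjust for it.

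With so few clusters, stable differences between hospitals are also the largest part of the error. Pre-training rates from the same hospital systems could remove much of that part, but only if the window is long enough and the comparison is fixed in advance. The plan settles neither.

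**Working it through.** **1. The plan's own figure.** Inputs from Sample size: "alpha error of 0.05, beta error of 0.20", 29 records per group before clustering, ICC 0.05, m = 8 wards × 6 months = 48. Design effect = 1 + (48 − 1) × 0.05 = 3.35. Then 3.35 × 29 = 97.15, rounded up to 98, and 98/48 = 2.04, so 3 hospitals per group. This reproduces.

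**2. Staffing, from Table 1 (secured plus non-secured).**

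| Hospital | Wards | Beds | Nurses | Nurses per bed |
|---|---|---|---|---|
| SZ | 11 | 668 | 315 | 0.472 |
| ST | 11 | 680 | 277 | 0.407 |
| GZ | 17 | 985 | 387 | 0.393 |
| HZ | 8 | 950 | 311 | 0.327 |
| MZ | 8 | 760 | 240 | 0.316 |
| FS | 9 | 922 | 272 | 0.295 |

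**3. All 20 allocations** (10 splits, each with two labellings).
- GZ, SZ and ST together: (387 + 315 + 277)/(985 + 668 + 680) = 979/2,333 = 0.420. The other three: 823/2,632 = 0.313. Ratio 1.34. This is 2 of 20 allocations, or 10%.
- Five of the ten splits, hence 10 of 20 allocations, differ by at least 15% in nurses per bed.
- Without the extreme split, the largest ratio is 1.17 (GZ, FS, MZ against the rest: 0.337 v 0.393).
- Ward type: GZ and ST have 3 non-secured wards each and the other hospitals 1 each. GZ and ST fall together in 8 of 20 allocations, which splits the 10 non-secured wards 7 v 3.

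**4. What a baseline buys, in SD units, on ICC 0.05 and m = 48.**
- Variance of a hospital's follow-up mean: 0.05 + 0.95/48 = 0.0698. The between-hospital share is 0.05/0.0698 = 72%.
- Unadjusted comparison: SE = √(2 × 0.0698/3) = 0.2157. With 4 df, half-width = 2.776 × 0.2157 = 0.60.
- With an equal 6-month baseline and a perfectly stable hospital effect, the baseline/follow-up correlation is r = 0.05/0.0698 = 0.72. This is the ceiling on these inputs.
- Hospital change: SE is multiplied by √(2(1 − 0.7164)) = 0.753. Half-width = 0.60 × 0.753 = 0.45, a cut of about 25%.

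**5. Dependence on baseline length.** With b baseline months and 8 wards, the SE ratio of change to follow-up only is √[(0.95/48 + 0.95/(8b))/0.0698].

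| Baseline months | SE ratio |
|---|---|
| 1 | 1.41 |
| 3 | 0.92 |
| 6 | 0.75 |
| 12 | 0.65 |

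Break-even is where 0.95/(8b) = 0.05, so b is about 2.4 months.

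**6. Cost of restriction.** The smallest two-sided p of an exact randomisation test is 2/20 = 0.10 unrestricted and 2/18 = 0.11 with the two allocations removed. A tighter rule, such as a staffing ratio of at most 1.10, keeps 10 allocations and gives 2/10 = 0.20. With 18 allocations each hospital is in the intervention arm in 9.

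**The case against.** **Follow-up is not said to be compared without baseline.** A reader might infer that the plan ignores baseline rates. The text does not say so. Effectiveness is assigned to a repeated ANOVA. If that includes T0, its group-by-time term compares change, and stable hospital differences cancel. Regression is left open. This objection stands: what can be said is that baseline adjustment of the primary comparison is not fixed.

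**Covariates are commonly left to an analysis plan.** This is fair for a condensed article, and an unseen plan may name them. It does not reach the allocation, which the article states completely and which precedes any analysis. Nor does it change the fact that the article names unadjusted group tests and sizes the trial on follow-up records alone.

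**Chance imbalance in prior WPV rate need not decide the result.** A reader might infer that it could. No hospital's rate is given. Take the planned change, "we set a significant change of 12.1% (decreased from 17.8% by 5.70" points, and an assumed between-hospital coefficient of variation (CV) around 17.8, so that the SE of the arm difference is 17.8 × CV × √(2/3). The chance of a baseline difference of at least 5.7 is then below 0.1% at CV 0.1, 5% at 0.2, 19% at 0.3 and 43% at 0.5. On the plan's own ICC, with the SD of 7.75 that 29 per group implies for a difference of 5.7, it is below 0.01%. The stronger claim is unsupported.

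**Size is not bias.** The outcomes are rates per patient day, so unequal bed and ward totals (39 v 25 wards in the extreme split) are not in themselves a distortion. Chance imbalance is also imprecision rather than bias, provided that hospital-level variance enters the test. Both points stand.

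**Larger precision gains are tempting.** A correlation of 0.8 would cut the half-width by 37%, but it exceeds the 0.72 ceiling for an equal six-month baseline on the plan's inputs.

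**Conclusion.** The point holds as a cheap improvement to the design. The draw is unrestricted, and 10% of allocations would separate the hospitals fully on staffing (0.420 v 0.313 nurses per bed, ratio 1.34), a factor that the article itself ties to WPV. No baseline-adjusted primary comparison and no pre-training window are committed to.

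The gain of about 25% in CI half-width rests on the plan's ICC of 0.05, 8 wards per hospital, an equal six-month baseline and fully stable hospital effects. It shrinks if hospital effects drift, and a one-month baseline would lose precision in a change analysis. The documents do not support saying that the planned analysis discards baseline, that hospital size biases the rates, or that prior WPV rates will determine the outcome.

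**What to change.** **(a) Analysis.** Define a pre-training window of at least about six months of monthly hospital data. State one primary comparison with hospital as the unit of inference: either follow-up rates adjusted for baseline rate and ward type (secured or non-secured), or each hospital's change in log rate from baseline. Cost: a short paragraph and extraction of past records. A change analysis keeps 4 df but loses precision if the window is shorter than about 2.4 months on the inputs above. A baseline covariate fitted at hospital level uses one of the 4 df.

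**(b) Allocation, if the draw has not been made.** List the 20 allocations, exclude at least the two that place GZ, SZ and ST together, and draw one at random from the remaining 18. Record the list and the rule. The worst staffing ratio falls from 1.34 to 1.17, and every hospital can still fall in either arm. Cost: the smallest exact two-sided p rises from 0.10 to 0.11, and further under tighter rules. Six hospitals cannot reach 0.05 in that test even unrestricted, so (b) complements (a) and does not replace it. If allocation is already done, (a) alone remains available.
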